### Procedures

At the enrollment phase, families will be screened for inclusion criteria in a telephone interview (see Fig. 1). If the study requirements are met, the adolescents and their caregivers will be informed about the study procedures during an initial contact meeting and will receive the consent form. External randomization will be performed by a researcher who is not involved in the study. All patients will undergo an initial clinical assessment to determine clinical parameters (e.g., weight, height, BMI, pulse). The therapists will discuss the initial FBT-interventions with the family and, after randomization, inform the family whether they will additionally receive guidance for FBT-HT or FBT-MBSR. After the initial interview, both the adolescents and their parents will receive a web-based link to an electronic test battery assessing psychopathology and interfamily relationships to be completed within 7 days. The study intervention will last 3 months. At the end of the treatment phase, the clinical staff will again collect clinical parameters, and another link to an electronic test battery will be sent. During the 3-month treatment phase, weight, blood pressure, and pulse will be recorded weekly. In addition, treatment progress is to be assessed by both patients and therapists after each FBT consultation. After 12 months, families will be contacted by email and asked to complete the final test battery.

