### Power analysis

The target sample size for the primary analysis was derived from an a priori power calculation using G*Power (version 3.1.9.7) and repeated measures ANOVA as a statistical model. Assuming a small effect size of *f* = 0.2, power of 80%, type 1 error level of *p* < 0.05 and correlation among repeated measures of *r* = 0.5, the necessary total sample size of 66 is adequate to test our main hypothesis involving three groups, two time points and the statistical interaction term. Assuming a reasonable attrition rate of 25%, we set our target sample to 90, equivalent to 30 participants per group, assuming equal treatment arm sizes. This number also aligns with the study feasibility, as it approximates the number of eligible patients who previously registered at the outpatient clinic over time intervals similar to the planned recruitment period of 3 years.

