### Data analysis plan

The initial descriptive statistics will summarize participant data characteristics as means, standard deviations, minima, maxima, frequencies and percentages. The validity of stratified randomization will be evaluated by inspecting between-group differences at baseline by means of a one-way analysis of variance (ANOVA), Kruskall–Wallis test or chi-squared test (in dependency of conventional statistical assumptions and the variable type, i.e., continuous versus categorical). Outcome data will be evaluated for the normality assumption by a combination of visual (Q–Q plots, histograms) and statistical (Shapiro–Wilk test) methods and will be transformed if necessary to meet the normality assumption. Participant characteristics of the analyzed sample and dropouts will be subjected to an additional inspection for possible non-random differences. Missing data will be handled by the maximum likelihood estimation method. The effects of the interventions will be assessed as changes in the primary outcomes from pre-test to post-test and follow-up assessment using EDE, EDI-2 and BMI analyzed with a repeated measures ANOVA followed by a post-hoc Tukey’s test to compare treatment means when there is a significant effect. The potential influence of confounding factors (age, premorbid BMI, duration of illness, age at onset, duration and setting of pre-treatment, medication use) will be further explored in sensitivity analyses. The secondary continuous variables will be analyzed in parallel. The measures related to treatment implementation (FBB, BPT) will be evaluated using descriptive statistics. Corrected effect sizes, expressed as Hedges’s *g* and significant deviations beyond the 95% confidence interval, will be computed for between- and within-group terms and will indicate empirical power estimates for a subsequent confirmatory study. Exploratory analyses will test the FB-K measure as a mediator/moderator of efficacy. To examine the FBT process, the ratings of each therapy session by the adolescents and the therapists will be compared and analyzed to assess their common development over time. More advanced statistical methods, such as generalized estimating equations (GEE) (which allow for more flexible modelling of the correlation structure among observations, are less sensitive to violation of assumptions and estimate population-wide average effects) will be also applied to assess differences in BMI percentiles and EDE/EDI-2 trajectories. The statistical significance threshold will be set to *p* < 0.05.

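### Randomisation is called stratified, but the primary ANOVA as written has no stratum term; if the strata predict change, the test is conservative and precision is lost

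*Protocol article*

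**What the plan says.** The Data analysis plan refers to stratification once: "The validity of stratified randomization will be evaluated by inspecting between-group differences at baseline". The Procedures section describes the allocation only as follows: "External randomization will be performed by a researcher who is not involved in the study". The Participants section adds that patients are randomly assigned to one of three treatments. Neither section mentions strata.

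The primary outcomes (EDE, EDI-2, BMI) are to be "analyzed with a repeated measures ANOVA followed by a post-hoc Tukey’s test to compare treatment means when there is a significant effect". The effect of interest is a change: "The effects of the interventions will be assessed as changes in the primary outcomes from pre-test to post-test and follow-up assessment". The only covariates named are kept out of the main analysis: "age, premorbid BMI, duration of illness, age at onset, duration and setting of pre-treatment, medication use) will be further explored in sensitivity analyses". None of them is identified as a stratification factor. Secondary continuous outcomes are to be analysed in the same way.

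**The concern.** When arms are balanced within strata, differences between strata no longer contribute to chance differences between arms. A model without the strata still leaves those differences in its error term. The standard error of the arm comparison is then larger than its true sampling variation, the test rejects less often than its nominal 5% under the null, and some of the precision that stratification could buy is not collected.

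This matters somewhat here because the sample is hard to enlarge. The Power analysis section says that 90 approximates the number of eligible patients who registered over periods similar to the planned three years of recruitment. Comparing the arms at baseline, the only use the article makes of the stratification, does not take stratum variation out of the error term.

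**Working it through.** **Inputs from the article.** Three groups, two time points, interaction test, f = 0.2, correlation r = 0.5, alpha 0.05, N = 66 before attrition, 25% attrition, target 90 in equal arms.

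**Input not in the article (assumption).** R², the share of the variance of *change* explained by the strata, taken as 0%, 10%, 20% and 30%. The calculation uses two equal strata.

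**1. The plan's own figure.** For the within-between interaction, λ = f²·N·m/(1 − r) = 0.04 × 66 × 2/0.5 = 10.56, with 2 and 63 degrees of freedom. Power is 81.8%; N = 63 gives 79.8%. So 66 reproduces as the smallest multiple of three that reaches 80%. Inflation gives 66/(1 − 0.25) = 88, consistent with 90.

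**2. Size without the strata.** With two time points, the group-by-time test is a one-way ANOVA on change. Scale the variance of change to 1. Under exact balance within strata, the arm means vary only through the part 1 − R², while the error mean square estimates roughly the whole. The F statistic is thus shrunk by a factor of about 1 − R². In large samples, size = P(χ²₂ > 5.991/(1 − R²)) = exp(−5.991/[2(1 − R²)]). The standard error is too large by 1/√(1 − R²).

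| R² on change | SE ratio | Size, large-sample | Size, simulated, N = 66 | Size, simulated, N = 90 |
|---|---|---|---|---|
| 0% | 1.00 | 5.0% | 5.1% | 4.7% |
| 10% | 1.05 | 3.6% | 3.5% | 3.7% |
| 20% | 1.12 | 2.4% | 2.4% | 2.4% |
| 30% | 1.20 | 1.4% | 1.4% | 1.5% |

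Each simulated value rests on 40,000 runs (Monte Carlo standard error about 0.1 percentage point). With the stratum in the model, size was between 4.9% and 5.1% throughout.

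**3. Level versus change.** Strata that explain 30% of the outcome level but none of the change gave 5.1% (N = 90) and 5.3% (N = 66), against 5% in theory. A constant stratum effect cancels in the change, so nothing is lost.

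**4. Imperfect balance.** Starting from 15 per arm per stratum and removing patients at random down to 66, the size is about 4%, 3% and 2% at R² of 10%, 20% and 30%. If nothing enforces balance within strata, it stays at about 5%.

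**5. Power at 66 completers.** With one arm ahead by 0.8485 SD of change and 22 per arm, λ = 22 × (2/3) × 0.8485² = 10.56, which is the planned effect. Adjusting for the strata raises λ to 10.56/(1 − R²), that is 11.73, 13.20 and 15.09.

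| R² on change | Power, strata omitted | Power, strata included |
|---|---|---|
| 10% | 82.1% | 85.8% |
| 20% | 83.5% | 89.8% |
| 30% | 84.3% | 93.6% |

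**The case against.** The strongest reply is that the article establishes none of the conditions for a loss. The word stratified appears once. No factor, block scheme or minimisation is described, and a condensed article may leave these to the full protocol. That stands: the missing names are not the point, and the consequence can only be stated conditionally. What remains is that the article describes its allocation as stratified, sets out the primary analysis, and places covariate adjustment outside it. Its list of terms may be incomplete, and some of the listed covariates could be the strata, but they would then still be only in sensitivity analyses.

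The upper R² values are also demanding. With two equal strata, the difference in change between them is 2√R²: 0.63, 0.89 and 1.10 SD. The last two exceed the 0.85 SD treatment lead used for power. Nothing in the article supports values that large. Some prediction of change is plausible, however: the trial enrols both full-syndrome patients and atypical patients whose BMI is unremarkable, and a stratum of that kind (an illustration only) could well predict BMI change.

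A reader might infer that the standard errors are in fact too wide and that the trial runs below 5%. The documents do not support this. At R² = 0, or without enforced balance, there is no shortfall. The figures are also per test: three primary outcomes are each tested against the threshold ("The statistical significance threshold will be set to *p* < 0.05"), with no correction stated. If they were independent at 5% each, the chance of at least one false positive would be 1 − 0.95³ = 14.3%. Nor is the planned power lost, since unadjusted power stays above 80% throughout.

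**Conclusion.** The point holds in conditional form. Stratified allocation is stated and the primary model as written does not use it. If allocation is balanced within strata and the strata predict change, the group-by-time test is conservative: about 3.5%, 2.4% and 1.4% per test at assumed R² of 10%, 20% and 30% with exact balance, and 5% at R² = 0. The price is forgone power of roughly 4 to 9 percentage points at 66 completers (85.8 − 82.1 = 3.7; 93.6 − 84.3 = 9.3). Validity is not at risk. This is a nearly free improvement and not an error that invalidates the analysis. Confidence is moderate, because neither the allocation scheme nor the predictive strength of the strata can be read from the article.

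**What to change.** State whether randomisation is stratified. If it is, include the stratification factors as fixed effects, with their interaction with time, in the primary models for EDE, EDI-2 and BMI and in the secondary models. The interaction is the part that matters, because a stratum main effect alone cancels in the group-by-time test. If randomisation is not stratified, delete the word from the Data analysis plan; the model needs no change on this account. Either way the cost is one sentence, plus a few degrees of freedom if the strata are added.

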## Methods

### Participants

Participants are to include a consecutive sample of 90 adolescents (aged 12–18 years) with full-syndrome AN or atypical AN (as well as their caregivers) that have been referred to the outpatient eating disorders unit at the Department of Child and Adolescent Psychiatry of the University Psychiatric Hospital, Zurich, Switzerland. Only patients with atypical AN who have all psychopathological symptoms of AN but whose percent mean body mass index (BMI) is clinically unremarkable according to the Centers for Disease Control and Prevention (CDC) growth charts [23] will be included in this study. Participants will be randomly assigned to one of three treatments (FBT, FBT-HT, FBT-MBSR). The inclusion criteria are as follows: (1) living with at least one adult caregiver,(2) willingness and ability to engage in family therapy; (3) being medically stable for outpatient treatment, as determined by a physician; (4) lack of comorbidities that contraindicate psychotherapy (e.g., psychosis); (5) an IQ greater than 75 (as determined by testing/clinical impression by a professional); (6) adequate German language skills; (7) residency within the Canton of Zurich, as outreach services necessary for two of the treatment groups are limited to this geographical region.

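### Normality is to be checked on the outcome data, not on within-person errors; for BMI, the AN/atypical-AN mix could prompt a needless transformation

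*Protocol article*

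**What the plan says.** All references are to the protocol article.

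- **Data analysis plan, object and tools of the check:** "Outcome data will be evaluated for the normality assumption by a combination of visual (Q–Q plots, histograms) and statistical (Shapiro–Wilk test) methods".
- **Data analysis plan, consequence:** the data "will be transformed if necessary to meet the normality assumption". The section names no transformation and no numerical trigger. It does not say whether untransformed results would also be shown.
- **Data analysis plan, primary analysis:** EDE, EDI-2 and BMI are "analyzed with a repeated measures ANOVA followed by a post-hoc Tukey’s test to compare treatment means when there is a significant effect".
- **Data analysis plan, further model:** generalized estimating equations (GEE) are to be applied as well, on the ground that they "are less sensitive to violation of assumptions and estimate population-wide average effects".
- **Participants:** the sample is a "consecutive sample of 90 adolescents (aged 12–18 years) with full-syndrome AN or atypical AN". The atypical patients are those "who have all psychopathological symptoms of AN but whose percent mean body mass index (BMI) is clinically unremarkable". The expected shares of the two subtypes are not given.
- **Effectiveness:** the weight outcome is named as a BMI z-score.

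**The concern.** The sentence fixes which quantity is inspected, and for the test of interest it is the wrong one. A repeated measures ANOVA does not need a normal pooled outcome. Its group-by-time test works on differences within persons, so a stable difference in level between patients drops out of it.

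In this trial such a difference is built in for BMI. One subtype has low weight and the other is defined by an unremarkable BMI, so the pooled values can form a two-component mixture. A histogram or Q–Q plot of those values shows the mixture just as a formal test does, so the visual checks give no protection.

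A non-linear transformation does not preserve an interaction. If BMI is re-scaled because of the subtype mixture, the group-by-time effect tested is no longer the difference in BMI (or BMI z-score) gain. A z-score also takes negative values, so a log or plain power transformation would need an arbitrary shift. At stake are some power and the scale on which the treatment effect is expressed.

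**Working it through.** **1. The plan's own figure.** The Power analysis section gives f = 0.2, 80% power, alpha 0.05, r = 0.5, three groups, two time points and the interaction. With λ = f²·N·m/(1−r), df1 = (3−1)(2−1) = 2 and df2 = (N−3)(2−1), N = 66 gives λ = 0.04 × 66 × 2 / 0.5 = 10.56 and power 0.818. The smallest N reaching 80% is 64, or 66 as a multiple of three. For attrition, 66/0.75 = 88, set to 90. The stated 66 reproduces, and the powered test is the interaction.

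**2. Why the offset cancels.** Write BMI for person i at time t as y(i,t) = subtype level + group-by-time mean + e(i,t). The change y(i,1) − y(i,0) contains no subtype level. With two time points, the interaction test is a one-way F test on that change. Normal errors therefore give a valid test whatever the pooled distribution looks like.

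**3. How often each quantity looks non-normal.** Assumptions: normal errors, r = 0.5, one third atypical, within-subtype SD 0.7, and BMI-z gaps of 1.5, 2.0 and 2.5 (divided by 0.7, these are 2.1, 2.9 and 3.6 SD). Share of simulated trials with Shapiro-Wilk p < 0.05 at n = 66:

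| Quantity tested | 2.1 SD | 2.9 SD | 3.6 SD |
|---|---|---|---|
| Raw baseline BMI | 17% | 54% | 92% |
| Baseline residuals from group-by-time cell means | 15% | 46% | 83% |
| Residuals of within-person change | 5% | 5% | 6% |

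Cell residuals still carry the subtype offset and fail almost as often as raw values. Over atypical shares of 20–33% at 2.9 SD, the rates are 49–63% against 57–69%. Only the change residuals behave as they should.

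**4. Effect on the interaction test.** Worst case for the trigger: a Shapiro-Wilk failure at either time point leads automatically to a transformation. One arm is shifted by δ within-subtype SDs. At r = 0.5 the SD of change is 1, so λ = 22 × (2/3) × δ² = 10.56 gives δ = 0.85, which matches the plan's f = 0.2. At n = 66:

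- *Yeo-Johnson transformation, 20–33% atypical:* power loss is about 0 points at 1 SD, 1 at 2.1 SD, 5 at 2.9 SD and 8–10 at 3.6 SD.
- *Box-Cox transformation of positive BMI-like values, 10–50% atypical:* the loss is at most 0.5 points at 1 SD and 0.4–2.7 at 2 SD. At 3 SD it is 8–12 points for a 10–30% share (for example 0.829 to 0.713 at 20%) and under 1 point at 50%.
- *Type I error:* about 5% throughout (0.041–0.065 with Box-Cox).
- *Changed significance decision (Box-Cox):* up to 13% of trials under the alternative and up to 2.5% under the null.

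The two runs agree up to about 2 SD. Near 3 SD the loss depends on the transformation chosen, which the article does not name.

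**5. If the subtypes gain different amounts.** With a 25% atypical share, a 3 SD gap and an average gain of 0.2 SD in atypical patients against 1.0 SD in the others, change residuals still fail in only about 5% of trials. Box-Cox power falls from 0.788 to 0.721, a loss of 6.7 points.

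**The case against.** The strongest reply is that the sentence describes a judgement, not an automatic rule. A reader might infer that a failed Shapiro-Wilk test by itself triggers a transformation. The text does not support this: the test is one part of a combined visual and statistical assessment, and transformation follows only where it is thought necessary. The failure rates above are therefore not transformation rates, and adding up tests over outcomes and time points would not make them so. This stands. It does not remove the point, because the visual checks are made on the same pooled data.

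A reader might also extend the mixture argument to EDE and EDI-2. The Participants section speaks against that: atypical patients are required to have the full psychopathology and differ in BMI. The mixture argument reaches BMI only.

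Nor does re-scaling take Hedges's g out of its units, since g is standardised and has none.

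Two further replies carry some weight. The choice of transformation, and whether original-scale results are also shown, can properly be left to a statistical analysis plan. What remains is the object of the check, which the article itself states. The planned GEE analyses also lower the stakes, but they are additional to the ANOVA and the article does not say that they use untransformed data.

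Finally, asking only for residuals of the fitted model would not be enough, because group-by-time cell residuals keep the subtype offset.

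**Conclusion.** The point holds in a narrow form and is minor. The article places the normality check on the outcome data, whereas the group-by-time test depends on within-person errors. For BMI, the planned mix of subtypes can make the pooled data look non-normal when those errors are normal, and a transformation would then change the scale of the interaction without need.

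A reader might infer that false-positive findings increase. They do not: type I error stays near 5% in every scenario examined. The cost is in power and in the scale of the effect. With 66 completers, a 20–33% atypical share and an automatic transformation, the power loss is negligible at a gap of 1 SD, about 1 point near 2 SD, about 5 points near 3 SD (8–12 with Box-Cox on positive values at a 10–30% share) and about 8–10 points at 3.6 SD. Subtype share, gap, within-subtype SD, transformation and automatic trigger are all assumptions. A more cautious use of the check would cost less.

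**What to change.** Replace the normality sentence in the Data analysis plan with wording to this effect:

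- The primary outcomes, BMI in particular, are analysed on their original scale.
- Normality is judged on the residuals of within-person change, or on conditional within-subject residuals, and not on raw values or on residuals from group-by-time cell means.
- If these residuals depart clearly from normality, robust or bootstrap confidence intervals are added.
- Any transformed analysis is reported as a sensitivity analysis and applied to all time points of that outcome.

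The change affects wording only and needs no new data or larger sample. The downside is slightly lower efficiency if an outcome proves strongly skewed.

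### The plan promises maximum likelihood for missing data, but the repeated measures ANOVA it names as primary model does not deliver this in its conventional form

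*Protocol article*

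**What the plan says.** Three statements in the Data analysis plan bear on this point.

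- Missing data: "Missing data will be handled by the maximum likelihood estimation method". No model, software or algorithm is attached to that sentence.
- Primary analysis: the outcomes are assessed as "changes in the primary outcomes from pre-test to post-test and follow-up assessment", and they are "analyzed with a repeated measures ANOVA followed by a post-hoc Tukey’s test to compare treatment means when there is a significant effect".
- Dropouts: "Participant characteristics of the analyzed sample and dropouts will be subjected to an additional inspection for possible non-random differences".

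GEE is added later in the same section as a more advanced method for BMI percentiles and for EDE and EDI-2 trajectories. No linear mixed model or other likelihood-fitted model is named.

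The Power analysis section uses repeated measures ANOVA as its model and plans for loss: "Assuming a reasonable attrition rate of 25%, we set our target sample to 90".

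Table 1 schedules EDE, EDI-2 and BMI at week 0, week 12 and 12 months. The Procedures section says that families are approached by email for the 12-month battery. It also says: "During the 3-month treatment phase, weight, blood pressure, and pulse will be recorded weekly".

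**The concern.** The sentence on missing data and the sentence on the model do not fit together. Maximum likelihood handles incomplete data through a model whose likelihood is built from whatever each patient contributed. The usual repeated measures ANOVA is a least-squares analysis that needs a full row per patient. An analyst who runs the named model with standard software therefore gets a complete-case analysis without having chosen one. An analyst who takes the missing-data sentence as binding has to fit a different model from the one named. The two would analyse different patients on the primary outcomes.

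The 12-month wave is where this is most likely to matter. It depends on families answering an email nine months after treatment ends, and in a three-wave ANOVA a non-response there also discards the patient's week-12 result. If the patients lost this way did systematically better or worse by week 12, and more so in one arm, the comparison of the groups as randomised is distorted.

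**Working it through.** **1. Which named model delivers maximum likelihood?**

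| Named method | Likelihood-based? | Patient with one missing wave |
|---|---|---|
| Repeated measures ANOVA, conventional form | No, least squares | Dropped |
| GEE, standard form | No, estimating equations | Observed visits kept, but in general valid only if data are missing completely at random or missingness is explained by covariates in the model |
| Likelihood-fitted mixed model | Yes | Observed visits kept; valid if missingness depends on observed data and the model is right |

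Only the third row matches the missing-data sentence, and the plan does not name it.

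**2. Is power lost?** Inputs from the Power analysis section: k = 3 groups, m = 2 time points, f = 0.2, correlation r = 0.5, alpha 0.05, power 80%. For the group-by-time interaction:

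- Non-centrality = f² × N × m / (1 − r), with df1 = (k − 1)(m − 1) = 2 and df2 = (N − k)(m − 1) = N − 3.
- N = 66: 0.04 × 66 × 2 / 0.5 = 10.56, power 0.818. N = 63: 10.08, power 0.798. So 66 is the smallest total with equal arms that reaches 80%, and the stated figure reproduces.
- Inflation: 66 / (1 − 0.25) = 88, rounded up to 90.
- Complete cases at 25% loss: 90 × 0.75 = 67.5. At N = 67, non-centrality = 10.72 and power = 0.824.

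On the plan's own inputs, a complete-case analysis still meets the 80% target.

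**3. How large could the bias be?** The documents give no dropout mechanism, so this is an illustration under assumed values: 30 per arm; SD 1 and correlation 0.5 between all three waves; one arm better by 0.5 SD (or 0) at week 12 and 12 months; loss of about 25% between week 12 and 12 months; 8,000 simulated trials per row. Where loss depends on outcome, the log-odds of leaving are −1.3 − 1.0 × (week-12 change). The complete-case estimate is the difference in mean change from baseline to 12 months. The likelihood-based estimate also uses the baseline and week-12 values of those who left. "One arm only" below means the comparator arm, with 25% random loss elsewhere.

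| Loss after week 12 | True difference | Complete-case | Likelihood-based |
|---|---|---|---|
| Completely random | 0.5 | 0.495 | 0.496 |
| Depends on week-12 change, same rule in all arms | 0 | 0.000 | 0.001 |
| Depends on week-12 change, same rule in all arms | 0.5 | 0.473 | 0.503 |
| Depends on week-12 change in one arm only | 0 | −0.102 | 0.006 |
| Depends on week-12 change in one arm only | 0.5 | 0.400 | 0.507 |

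The complete-case error with a true difference of 0.5 is 0.5 − 0.473 = 0.027 under a common rule and 0.5 − 0.400 = 0.100 when the rule applies in one arm. The standard error of either estimator is about 0.30, so 0.10 is about one third of a standard error. With the one-arm rule the complete-case analysis also shows a difference of about 0.10 SD where none exists.

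**The case against.** The best defence is that the plan nowhere says that incomplete patients are excluded; it says the opposite in intent. Maximum likelihood could be meant through a likelihood-fitted repeated measures model or through EM estimates, and a condensed article may leave that to a fuller document. This stands as far as it goes: complete-case analysis is inferred from the usual form of the method. It does not settle the matter, because the article names a specific primary model, and that model as commonly run contradicts the stated handling. If gaps were instead filled by EM and an ordinary ANOVA run on the result, filled values would be treated as observed and standard errors would be too small.

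Four stronger readings are tempting, and the documents do not support them.

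- *Completers are confirmed as the analysed set.* Contrasting analysed patients with dropouts is a common descriptive check, and raising 66 to 90 is routine whatever the model. Both are consistent with a completer analysis; neither establishes one.
- *Every patient missing one of three waves is certainly lost.* This assumes a single three-wave ANOVA. The Power analysis section describes two time points, and a separate baseline-to-week-12 test would keep patients lost only at 12 months.
- *The weekly weights go unused for efficacy.* The plan assigns them no role, but it does not say which visits the GEE will use.
- *Changing the model cures early dropout as well.* An illustrative two-arm simulation (true difference 0.86 SD, 27–29% loss before week 12 driven by week-4 and week-8 change, variances assumed) gives 0.82 for completers, 0.82 for likelihood on weeks 0 and 12 alone, and 0.86 once weeks 4 and 8 are added. With stronger dependence the figures are 0.75, 0.77 and 0.86. There the change of model recovers only (0.77 − 0.75) of (0.86 − 0.75), about one sixth to one fifth of the bias. The rest comes from interim weights, and Table 1 schedules no interim EDE or EDI-2.

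**Conclusion.** The point holds in this form: neither the repeated measures ANOVA in its conventional least-squares form nor GEE delivers the maximum likelihood handling that the plan states. It would go too far to say that the promised protection does not exist. It is not delivered by the model as named.

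The consequence is possible bias, not loss of power. The illustrated size is about 0.03 to 0.10 SD at 12 months. It rests on an assumed correlation, an assumed link between week-12 change and dropout, and loss occurring after week 12. If loss is completely random, the bias is nil. That patients with poor weight gain are the ones who leave is plausible, but the documents do not say so. A likelihood-based model protects only as far as missingness depends on observed data. The correction is worth making because the choice decides which patients enter the primary comparison.

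**What to change.** In the Data analysis plan, replace the repeated measures ANOVA as primary model by a linear mixed model for repeated measures fitted by REML, with arm, visit and arm-by-visit terms. Fit it to all observed visits of all randomised patients in their assigned arm. Pre-specify the covariance structure; with three scheduled visits an unstructured form is feasible. Label GEE as a sensitivity analysis. The missing-data sentence then describes what the primary model does.

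If the ANOVA is kept, the least that is needed is a statement of how maximum likelihood enters it and whether patients with a missing wave are in the primary analysis.

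Optional, for BMI z-score only: include the weights already recorded weekly during the treatment phase, so that patients who leave before week 12 still contribute. This cannot be done for EDE or EDI-2.

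The cost is wording and analysis code, with no new data and no change to the sample size. The small downside is that a covariance model must be fixed in advance, ideally before any comparison by arm.

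### The primary repeated measures ANOVA compares change from baseline and no stated analysis adjusts for baseline: the test is valid, but less efficient than the collected data allow

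*Protocol article*

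**What the plan says.** The Data analysis plan section assesses the interventions as "changes in the primary outcomes from pre-test to post-test and follow-up assessment using EDE, EDI-2 and BMI analyzed with a repeated measures ANOVA", with Tukey comparisons after a significant result. The Power analysis section uses the same model, an "a priori power calculation using G*Power (version 3.1.9.7) and repeated measures ANOVA as a statistical model", and names the tested term: "three groups, two time points and the statistical interaction term". It assumes f = 0.2, 80% power, a "type 1 error level of *p* < 0.05" and a "correlation among repeated measures of *r* = 0.5", and concludes that "the necessary total sample size of 66 is adequate to test our main hypothesis".

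The covariates for the sensitivity analyses are listed: "The potential influence of confounding factors (age, premorbid BMI, duration of illness, age at onset", followed by pre-treatment and medication. Baseline EDE, baseline EDI-2 and study-entry BMI are not among them. Premorbid BMI is a different variable, and Table 1 lists it separately from the BMI outcome. GEE models of trajectories are planned as well, with no baseline adjustment named. Table 1 shows all three primary outcomes collected at week 0.

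**The concern.** When the pre-test value is one level of the time factor, the group-by-time test for baseline against one later wave is the same as a one-way ANOVA of change scores. That fixes the slope of follow-up on baseline at 1. Under the plan's own correlation, with equal SDs, the slope is 0.5. The change score therefore over-corrects: part of any chance baseline difference between arms stays in the estimated effect, with the opposite sign, and appears as extra variance.

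This matters because the arms are small (30 randomised, about 22 after the assumed attrition) and recruitment is limited by referrals over three years. Precision available from data already collected costs almost nothing.

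**Working it through.** **Inputs.** From the Power analysis section: k = 3 groups, m = 2 time points, f = 0.2, r = 0.5, alpha 0.05, N = 66, 25% attrition, target 90. The protocol gives no SDs, so equal SDs at the two waves is an assumption, varied below.

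**1. The plan's own figure.** For the within-between interaction, lambda = N·m·f²/(1 − r) = 66 × 2 × 0.04 / 0.5 = 10.56, with 2 and 63 df. Power is 0.818 (0.798 at N = 63), so 66 is the smallest total in three equal groups that reaches 80%. Attrition: 66/0.75 = 88, so a target of 90 is consistent.

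**2. Variance with and without baseline adjustment** (equal SDs, in units of SD²).
- Change score: 2(1 − r) = 2 × 0.5 = 1.00.
- Adjusted for baseline (ANCOVA): 1 − r² = 1 − 0.25 = 0.75.
- Ratio: (1 + r)/2 = 0.75, a saving of 25%. In standard error, √0.75 = 0.866, a saving of about 13%.

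A simulation of 20,000 trials with 22 per arm and the slope estimated gave a ratio of 0.76, so the realised saving is slightly smaller.

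**3. Power with adjustment at N = 66.** lambda = 10.56/0.75 = 14.08, with 2 and 62 df. Power is 0.917.

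**4. Dependence on r (equal SDs).** Saving = 1 − (1 + r)/2.

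| r | Saving in variance |
|---|---|
| 0.3 | 35% |
| 0.5 | 25% |
| 0.7 | 15% |
| 0.9 | 5% |

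**5. Dependence on the SD ratio (r = 0.5).** Let q be the follow-up SD divided by the baseline SD. Change variance is 1 + q² − 2rq = 1 + q² − q. Adjusted variance is q²(1 − r²) = 0.75q².

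| q | Change | Adjusted | Saving |
|---|---|---|---|
| 0.8 | 0.84 | 0.48 | 43% |
| 1.0 | 1.00 | 0.75 | 25% |
| 1.2 | 1.24 | 1.08 | 13% |
| 1.5 | 1.75 | 1.6875 | 4% |

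**6. What the lost variance is.** At r = 0.5 and equal SDs, the excess is 1.00 − 0.75 = 0.25 = (1 − r)² times the baseline variance. This is exactly the contribution of chance baseline imbalance. The SD of a pairwise chance gap is √(2/n): 0.26 outcome SD at 30 per arm and 0.30 at 22. Half of it, 0.13 to 0.15 SD, typically stays in the change-score effect. The simulated slope of the effect on the gap was −0.500 for change scores and about 0 for ANCOVA.

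**7. If answers shift with knowledge of the arm.** The Procedures section has families told their arm after randomization, and the web battery follows the initial interview with 7 days to complete it. Take an assumed 0.3 SD shift in one arm, r = 0.5 and no true effect.

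| Shift present at | Bias, change score | Bias, ANCOVA |
|---|---|---|
| Baseline only | −0.30 | −0.5 × 0.3 = −0.15 |
| Both waves | 0.00 | (1 − 0.5) × 0.3 = 0.15 |

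**The case against.** The strongest reply is that nothing here is wrong in the sense of invalid. The planned test keeps its type I error, is unbiased over repeated randomisations, matches its own power calculation and reaches the stated 80%. All of that stands. A reader might infer from the lost precision that the trial is underpowered or its result biased; the documents do not support that.

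The size is also open to challenge, and rightly. A quarter is one point in a wide range. The protocol gives no SDs, and BMI may correlate over time more strongly than 0.5, in which case the gain for BMI could be near 5%.

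It is tempting to count lost precision and chance baseline gaps as two harms. Step 6 shows that they are one quantity, already in the test's standard error. A gap as large as 0.5 SD would also be uncommon: for a given pair, about 5% at 30 per arm and 10% at 22.

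A reader might also infer that switching to baseline adjustment is free of risk. It is not. If knowing the arm shifts answers at both waves, the change score cancels the shift and ANCOVA keeps part of it; if only at baseline, ANCOVA does better. Neither method dominates.

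Finally, the article is condensed, the GEE terms are unspecified and an analysis plan may add covariates. That limits the claim to what is stated. It does not remove the point, because the primary model, its tested term and the sensitivity covariates are all named.

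**Conclusion.** The point holds as one of efficiency. The stated primary analysis compares change from baseline, and no stated analysis adjusts for the baseline value of the outcome. At r = 0.5 with equal SDs, adjustment would save about 25% of the variance (about 13% of the standard error, slightly less with the slope estimated at 22 per arm), and power at N = 66 would be about 0.92 instead of 0.818. Under the other inputs examined, the saving runs from 4% to 43%. The figures are exact for baseline against one later wave, which is the comparison the trial was sized on. The change is worth making, but the trial's validity does not depend on it.

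**What to change.** In the Data analysis plan section, make the week-12 and 12-month values the outcomes of a maximum likelihood longitudinal model with arm, time, arm by time, and the baseline value of the same outcome with a slope for each time point. Report baseline-adjusted arm differences at each time point. Use the same model for the secondary continuous outcomes, and keep the sample size.

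For EDE and EDI-2, either have the baseline battery completed before the arm is disclosed, or keep the change-score analysis as a sensitivity analysis. A longitudinal model that constrains arm means to be equal at baseline is an alternative only with the same caution, since answers given after disclosure may violate that constraint.

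Cost: analysis wording and one degree of freedom per covariate, with no new data and no more patients. If the order of baseline collection is changed, there is also a procedural change.
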